# A randomized controlled phase III study comparing hadrontherapy with carbon ions versus conventional radiotherapy – including photon and proton therapy – for the treatment of radioresistant tumors: the ETOILE trial

**DOI:** 10.1186/s12885-022-09564-7

**Published:** 2022-05-23

**Keywords:** Radiotherapy, Carbon ion therapy, Proton therapy, Photon therapy, Radioresistant tumors

## Abstract

**Background:**

Some cancers such as sarcomas (bone and soft tissue sarcomas) and adenoid cystic carcinomas are considered as radioresistant to low linear energy transfer radiation (including photons and protons) and may therefore beneficiate from a carbon ion therapy. Despite encouraging results obtained in phase I/II trials compared to historical data with photons, the spread of carbon ions has been limited mainly because of the absence of randomized medical data. The French health authorities stressed the importance of having randomized data for carbon ion therapy.

**Methods:**

The ETOILE study is a multicenter prospective randomized phase III trial comparing carbon ion therapy to either advanced photon or proton radiotherapy for inoperable or macroscopically incompletely resected (R2) radioresistant cancers including sarcomas and adenoid cystic carcinomas.

In the experimental arm, carbon ion therapy will be performed at the National Center for Oncological Hadrontherapy (CNAO) in Pavia, Italy. In the control arm, photon or proton radiotherapy will be carried out in referent centers in France.

The primary endpoint is progression-free survival (PFS). Secondary endpoints are overall survival and local control, toxicity profile, and quality of life. In addition, a prospective health-economic study and a radiobiological analysis will be conducted.

To demonstrate an absolute improvement in the 5-year PFS rate of 20% in favor of carbon ion therapy, 250 patients have to be included in the study.

**Discussion:**

So far, no clinical study of phase III has demonstrated the superiority of carbon ion therapy compared to conventional radiotherapy, including proton therapy, for the treatment of radioresistant tumors.

**Trial registration:**

ClinicalTrials.gov identifier: NCT02838602. Date of registration: July 20, 2016. The posted information will be updated as needed to reflect protocol amendments and study progress.

**Supplementary Information:**

The online version contains supplementary material available at 10.1186/s12885-022-09564-7.

## Background

Radiotherapy is improving rapidly and is being enhanced by innovative high-technology equipment using hadrontherapy by proton and carbon ion beams to destroy tumours [1, 2]. Compared to photons (X-rays), a beam of heavy charged particles (protons and carbon ions) enables significantly higher ballistic accuracy with the expected therapeutic benefit of an improvement of quality of life and chances of recovery [3].

Inherently mediocre ballistics selectivity of photons can be compensated by the use of a large number of beams (multiplication of entrance portals) and by modulation of the intensity of the beam enabling the dose to be accurately conformed to the target volume, with the main consequence of irradiating a much larger volume of healthy tissue to medium and low doses. This technique is used for innovative methods of photon radiation therapy: intensity-modulated radiation therapy (IMRT) using either advanced linear accelerators or specific tomotherapy devices and, for small volume tumors, stereotactic radiotherapy using either a conventional linear accelerator specially equipped or a dedicated mini-accelerator mounted on a robotic arm (the Cyberknife®).

Carbon ions also have a much higher biological efficiency (cell destruction) at the Bragg peak (and not in the entrance channel) at the same physical dose than so-called low linear energy transfer (LET) radiation, such as photons and protons [4, 5]. This relative biological effectiveness (RBE) is variable depending on the tissues passed through and is markedly higher for radioresistant cancers [6]. This intrinsic radiological property is the main argument for the use of carbon ions compared to protons.

Carbon ion radiotherapy has shown promising results for a variety of malignancies in prospective phase I/II or phase II studies [4, 7]. In particular, the medical benefit of carbon ions is expected to be major for non-operable (or incompletely resected) localized cancers that are radioresistant to low LET (photons and protons) and located near radiosensitive organs at risk. However, high level evidence from phase III studies demonstrating the benefit of carbon ions is not available [5, 8].

Certain types of cancers are known for their intrinsic radioresistance (melanomas, some sarcomas, adenoid cystic carcinomas) and are thus the main indications of carbon ions. Other types of cancers that are more frequent (e.g., squamous cell carcinomas, adenocarcinomas) may have extremely variable radiosensitivity, linked in particular to the existence of tumor hypoxia, but also to intrinsic biological characteristics that are still poorly understood and difficult to prospectively identify.

In the present study, two groups of indications known for their intrinsic radioresistance and for which the medical data obtained in the pioneering centers for carbon ion therapy are the most documented will be considered: sarcomas [9, 10] and adenoid cystic carcinomas of the head and neck [11–14]. Spinal and sacral chordomas and chondrosarcomas are dully included, but similar tumours of the base of the skull are currently the subject of randomized phase III studies comparing protons and carbon ions, and are thus excluded from the indications of the present study [15, 16].

We set up a multicenter randomized phase III study aimed at evaluating the clinical benefit of hadrontherapy based on carbon ions compared to the best modalities of photon radiation therapy or protons in these radioresistant tumors.

## Methods and design

### Study design

The ETOILE trial is a multicenter open-label randomized parallel-group superiority trial comparing carbon ion therapy with standard radiotherapy, including a treatment by photons or protons. Patients will be enrolled in French reference centers for cancer treatment. Patients fulfilling the eligibility criteria will be randomized into two arms using a 1:1 ratio (experimental arm: carbon ion therapy; control arm: photon or proton therapy). Follow-up takes place 2 months and 6 months after the end of radiotherapy, then every 6 months during 5 years.

### Study objectives and endpoints

The primary outcome is the progression-free survival (PFS) defined as the time from randomization to the first relapse or death, whatever the cause, or to the latest news date. Progression is defined according to RECIST v1.1 criteria [17] based on standard medical imaging (CT or MRI), and confirmed 6 months later. An independent committee unaware of the treatment group will validate all progressions.

Secondary outcomes include: the tolerance profile assessed using CTCAE-V4.02 grades; survival without locoregional progression; survival without metastases; overall survival; quality of life using the EQ-5D-3L. Associated health-economic and radiobiological studies are also planned.

### Patient selection

#### Inclusion/randomization criteria

Patients eligible for inclusion in this study have to meet all of the following criteria:age ≥ 18 yearsunresectable or inoperable cancer or a cancer with a macroscopically incomplete resection (R2)radioresistant cancers including: adenoid cystic carcinomas of the head and neck (excluding laryngeal and tracheal sites), soft tissue sarcomas, rhabdomyosarcoma of pleomorphic type only, retroperitoneal sarcomas providing technical feasibility, osteosarcomas of any localization and whatever the grade (Ewing’s sarcomas excluded), chondrosarcoma (excluding skull base) of WHO grade ≥ 2, chordomas of the axial skeleton and the pelvis (base of the skull excluded), and angiosarcomas (scalp angiosarcoma excluded).absence of epidermal invasion (a hypodermic invasion is accepted with cutaneous adherence but no permeation of the epidermis);largest dimension of the macroscopic volume (Gross Tumor Volume, GTV) < 20 cm;Performance Status ECOG ≤2 or Karnofsky Index ≥60;no severe comorbidities and life expectancy over 10 years;patient physically and mentally able to accept and receive cares far from their home;no ongoing pregnancy or risk of pregnancy for women of childbearing age;patient affiliated with a social security insurance;written informed consent to participate in the study.

Additional criteria are requested for randomization:validation of an indication for radiotherapy by a specialized local multidisciplinary tumor board (MTB) and, in the context of the indications of this study, validation of the indication and the feasibility for carbon ion therapy by the medical team of the National Center for Oncological Hadrontherapy (CNAO) in Pavia, Italy;possibility of offering carbon ion therapy within 2 months.

#### Non-inclusion/non-randomization criteria

Patients eligible for this study must not meet any of the following criteria:macroscopically or microscopically complete surgical excision (R0 or R1);a history of radiotherapy on the site and region to be treated;metastatic disease;disease not relevant for a curative approach (e.g. a very advanced disease with extensive regional invasion or with accelerated progression resistant to all medical treatments, especially sarcomas);contra-indication to the realization of a radiotherapy (by photons, protons or carbon ions) for medical or technical reasons;pre-scheduled surgery or chemotherapy after radiotherapy;a history or concomitant presence of another cancer; with the exception of an in situ cervical cancer or curatively treated basal cell cutaneous carcinoma or any other curatively treated cancer without signs of a relapse for at least 5 years;simultaneous participation in another prospective trial;patient unable to be followed-up for 5 years.

### Randomization

Randomization will be done using an Interactive Web Response Systems (IWRS). Stratification parameters include the center and the type of cancer (adenoid cystic carcinoma versus sarcoma and chordoma). As the trial design is open-label, no blinding of treatment assignment is possible.

### Reference committee

An Independent Data Safety Monitoring Board (IDSMB) is established to ensure the protection of patients, to ensure that the study is conducted in an ethical manner, to systematically reassess the benefit-risk balance of the trial and to ensure the independent review of the scientific results under study. The IDSMB will be composed of independent experts in the field of radiation oncology and methodology of clinical trials.

### Radiation therapy

#### Experimental arm: carbon ion therapy

In the carbon ion arm, patients will not receive conventional radiotherapy. For all patients randomized in this treatment arm, carbon therapy will be delivered at the CNAO in Pavia, Italy. The total duration of treatment will be 4 weeks (16 sessions, 4 sessions per week). Patients will receive support from the study team and the local team for their transportation and housing.

#### Control arm: standard photon or proton therapy

Patients will be able to receive two different types of radiotherapy in the control arm (photon or proton therapy). Standard treatment will be delivered in French regional centers for cancer treatment and university hospital centers, some private centers, and proton therapy centers.

Radiotherapy with intensity modulation (IMRT) will be delivered using most advanced procedures in the center recruiting the patients, after one or more preparation sessions (scanner, simulation and implementation under machine, verification by quality control imaging). The IMRT solution will be left to the investigator’s choice (standard IMRT, dynamic arctherapy, tomotherapy) according to local technical availability and the clinical situation. 3D conformal radiation therapy without intensity modulation will also be an option if it allows dosimetric results comparable to those of IMRT on the basis of the resulting dose-volume-histograms (DVH). All recommended technical modalities in terms of contention, repositioning capacity and quality control for image-guided radiation therapy (IGRT) will be implemented. Planned and performed treatment data will be recorded according to the current recommendations of the International Commission on Radiation Units and Measurements (ICRU).

Deep proton therapy will be performed only for some patients based on quantitative criteria for probable differences in normal tissue complication probability (NTCP) calculated by comparing a photon treatment plan with a proton treatment plan. The indication of proton therapy may result from the observation of an excessive toxic risk with photon therapy. Proton therapy can be exclusive or complementary to a photon therapy treatment when a low-risk volume is defined and substantially greater than the high-risk volume. In cases of photon-proton association, the proton part will be carried out first in order to give it the maximum of possibilities to adapt to the anatomical constraints without being disturbed by previously received doses. The use of proton therapy will be decided using an objective approach described in Fig. 1.

**Fig. 1 Fig1:**
[figure not shown]
Choice between photon and proton therapy in the control arm. ΔNTCP, Difference in normal tissue complication probability; LOAR, Dose limits of organs at risk; OAR, Organs at risk; RD, Recommended doses

This strategy will offer the opportunity to scientifically evaluate the feasibility and relevance of this approach based on NTCP models [18].

#### Dose prescription

In the experimental arm, the carbon ion therapy will be delivered according to the methods of the National Institute of Radiological Sciences (NIRS), Japan, and the Heidelberg Ion-Beam Therapy Center (HIT), Germany, adapted by the CNAO. As an indication, doses of carbon ion therapy to deliver are given in Table 1.

**Table 1 Tab1:** Experimental arm (carbon ion therapy)

Diseases	Methods	Doses (Gy (IsoE))^b^
Adenoid cystic carcinomas	CNAO^a^	60.8 to 64.0
Sarcomas	CNAO^a^	70.4 to 73.6
Chordomas	CNAO^a^	70.4 to 73.6

^a^adapted from the experience of NIRS, National Institute of Radiological Sciences (Japan) and HIT, Heidelberg Ion-Beam Therapy Center (Germany)

^b^All treatments are delivered in 16 fractions, 4 fractions per week

CNAO, National Center for Oncological Hadrontherapy; IsoE, Isoeffective dose to ^60^Co or Rx doses delivered with 2 Gy per fraction

For patients included in the standard arm (photon or proton therapy), minimum recommended doses are given in Table 2.

**Table 2 Tab2:**
[figure not shown]
Control arm (standard photon or proton therapy)

*CTV* Clinical target volume, *EQD2* Equivalent dose with 2 Gy per fraction, *GTV* Gross tumor volume, *IMRT* Intensity-modulated radiation therapy, *MGH* Massachusetts General Hospital

These dose recommendations are given for information purposes and are likely to change over time.

### General organization

A central platform from the Heidelberg Institute for Radiation Oncology (HIRO), the so-called *HIRO-ULICE platform*, will be used for storage and exchange of data such as anonymized medical imaging and patient medical records. This platform will allow the review of patient documents by proton centers for patients in the standard group requiring proton therapy, the confirmation by CNAO that carbon therapy is feasible, and a quality control by the study team. Figure 2 presents the workflow.

**Fig. 2 Fig2:**
[figure not shown]
Workflow diagram. ACC, Adenoid cystic carcinomas; CNAO, National Center for Oncological Hadrontherapy; MTB, Multidisciplinary tumor board

The Ennov Clinical trial software (version 8.2.50) will be used for randomization, clinical data collection, and central data management.

### Sample size calculation

The study is calibrated to detect a treatment effect hazard ratio (HR) of 0.515 under the proportional hazards assumption, translating in an absolute improvement of the 5-year PFS rate of 20% in favor of the experimental arm (70% in the experimental arm vs 50% in the control arm).

A total of 92 events [East Software- Copyright@Cytel inc. 1994] notified in the study would have 90% power to show statistically significant PFS at a 2-sided alpha. Considering initial recruitment duration of 24 months and a 5-year follow-up for the last included patient, 108 patients per arm would be randomized in the study. To optimize the study and consider the possibility of withdrawal of consent and patients lost to follow-up, the recruitment objective was set at 250 patients.

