#### Interim analysis

An interim analysis is planned for effectiveness or futility. This analysis will be carried out when approximately 50% (46 events) of the final number of PFS events has been reached. The significance level at this interim analysis to establish the superiority or futility of experimental treatment over control with regard to PFS will be determined based on the observed number of events, using the O’Brien & Fleming boundaries as implemented by the Lan-DeMets alpha spending method (Lan and DeMets 1983) in order to control the overall Type I error rate.

Using planned enrollment rate, this analysis should be performed 42 months after first included patient. For example, if the number of events at the time of interim efficacy analysis is exactly 46, the bounds to use during this analysis according to Lan Demets rules will be *p* = 0.0031 and *p* = 0.8443 respectively to reject H0 and H1.

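### At a two-sided alpha of 5%, 92 events give about 88–89% power, not the stated 90%; with the planned futility look, 90% needs about 98 events (minor)

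*Protocol article*

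**What the plan says.** Sample size calculation (protocol article): "The study is calibrated to detect a treatment effect hazard ratio (HR) of 0.515 under the proportional hazards assumption", which corresponds to 5-year PFS of "70% in the experimental arm vs 50% in the control arm". The target is "A total of 92 events", which "notified in the study would have 90% power to show statistically significant PFS at a 2-sided alpha". The sentence stops there without a number for alpha. Assuming 24 months of recruitment and 5 years of follow-up for the last patient, "108 patients per arm would be randomized in the study"; recruitment is then raised to 250 to allow for withdrawals and losses.

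Interim analysis: "An interim analysis is planned for effectiveness or futility", at 46 events, with O'Brien-Fleming boundaries by Lan-DeMets spending. If exactly 46 events are available, the bounds "according to Lan Demets rules will be *p* = 0.0031 and *p* = 0.8443 respectively to reject H0 and H1".

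Study design: 1:1 allocation. Visits take place 2 and 6 months after radiotherapy, "then every 6 months during 5 years".

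**The concern.** The standard event formula for a log-rank test at 5% two-sided, hazard ratio 0.515 and 90% power does not return 92. The planned interim cannot make up the difference: with the maximum number of events fixed, an interim look can only leave power unchanged or lower it.

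The event count also drives other figures. The interim trigger (46) is half of 92, and the futility bound is calibrated to a 10% type II error that 92 events do not quite deliver.

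A second, smaller matter is follow-up. The sizing assumes 5 years for the last patient, so 5 to 7 years per patient. The visit schedule can be read as ending for everyone at 5 years. The expected number of events depends on which is meant.

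**Working it through.** **Inputs.** Hazard ratio 0.515, 5-year PFS of 50% and 70%, 92 events, 108 per arm, 24 months of recruitment, 5 years for the last patient, 250 recruited (Sample size calculation); 1:1 allocation (Study design); one look at 46 events with bounds 0.0031 and 0.8443 (Interim analysis). The hazard ratio agrees with the PFS rates: ln 0.70 / ln 0.50 = 0.5146.

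**1. Recovering alpha.** O'Brien-Fleming-type spending at half the information, with 0.025 per side, spends 2 × [1 − Φ(2.2414/√0.5)] = 0.001525 per side. That is 0.00305 two-sided (Z = 2.963) and matches the stated 0.0031. So alpha is 0.05 two-sided.

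**2. Reproducing the futility bound.** The same spending shape with beta = 0.10 uses 2 × [1 − Φ(1.6449/√0.5)] = 0.0200 at the interim. With ln 0.515 = −0.6636, the mean of Z at 46 events is (√46/2) × 0.6636 = 2.250. The bound is Z = 2.250 − 2.054 = 0.197, a two-sided p of 0.844, against 0.8443 stated. The interim bounds are therefore consistent with a total of 92 and a nominal beta of 0.10.

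**3. Events for 90% power, single analysis (Schoenfeld).** 4 × (1.960 + 1.2816)² / 0.6636² = 95.4, so 96 events. Freedman's formula gives 103.

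**4. Power at 92 events, single analysis.** Φ[(√92/2) × 0.6636 − 1.960] = Φ(3.182 − 1.960) = 0.889.

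**5. Power with the interim.** Bivariate normal integration with correlation √0.5 and an interim efficacy bound of Z = 2.963. The final critical value is 1.9686 (p = 0.0490), or 1.958 for the binding case at 92 events.

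| Total events | Efficacy bound only | Binding futility | Non-binding futility |
|---|---|---|---|
| 92 | 88.8% | 88.5% | 88.3% |
| 96 | 90.1% | 89.7% | 89.5% |
| 97 | 90.4% | 89.98% | 89.8% |
| 98 | 90.6% | 90.3% | 90.04% |

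A log-rank simulation (20,000 trials, 108 per arm, 92 events) gave 88.5% for a single analysis and 88.3% with the efficacy look, in line with the table.

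**6. Futility bound at 98 events.** With 49 events at the interim, (√49/2) × 0.6636 = 2.323; the bound is 2.323 − 2.054 = 0.269, a two-sided p of 0.788.

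**7. Expected events.** Assumed: exponential PFS with yearly hazards ln 2/5 and −ln 0.70/5, and uniform accrual over 24 months.
- 216 patients, common cut-off at month 84, no losses: 60.8 + 37.5 = 98.4 events. The count reaches 92 at month 77.6 and 98 at month 83.6.
- 216 patients, each censored at 5 years, no losses: 108 × (0.50 + 0.30) = 86.4 events.
- 250 patients, each censored at 5 years, no losses: 125 × 0.80 = 100.0 events.
- 250 patients with losses. No rate is stated, so 1% to 5% a year is assumed: 97.8 to 89.3 events with the 5-year limit, and 110.9 to 99.7 with the common cut-off.

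**The case against.** The strongest reply is that the gap is too small to matter. At 92 events, 90% power is reached at a hazard ratio of 0.509 instead of 0.515, a difference well inside the uncertainty of the assumed PFS rates. The two interim bounds fit 92 events, and the inputs to the sizing software are not shown. The smallness of the gap stands, and it is why this is a minor point. The agreement of the bounds does not rescue the 90%, however: it shows that the futility bound was set for a 10% type II error, while the type II error at 92 events is about 11% to 12%.

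The missing alpha is a reporting gap in a condensed article, and the reader can recover it from the interim bound.

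A reader might go further and infer that the planned patients cannot supply 92 events, because 108 per arm followed for 5 years give only 86. The document does not support that. The sizing rests on 5 years for the last patient, which gives about 98 events from 216 patients. The Primary endpoint section censors event-free patients at last news and sets no 5-year limit. Moreover, 250 patients are to be recruited, and even with a 5-year limit they would give 100 events before losses. What remains is a difference in wording between the visit schedule and the sizing assumption.

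**Conclusion.** The stated 90% is slightly too high. At 5% two-sided and hazard ratio 0.515, 92 events give 88.9% power in a single analysis and 88.3% to 88.8% with the planned interim. The shortfall is 1.1 to 1.7 percentage points; closing it takes 96 events without futility stopping or about 98 with a non-binding futility bound.

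This rests on proportional hazards, on alpha inferred from the interim bound, and on O'Brien-Fleming-type spending for futility, which reproduces the stated bound. The article does not say whether futility is binding, and the answer moves power by only 0.2 points. The event projections also assume exponential PFS and uniform accrual.

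The point is minor. There is no bias and no inflation of type I error, and it does not show that the trial is materially underpowered or short of patients. The follow-up question comes down to reconciling two sections.

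**What to change.** 1. State alpha as 0.05 two-sided in the Sample size calculation section.
2. Then choose one of two options:
   - keep 92 events and restate power as about 88%, a change of wording only; or
   - set the target at 98 events, with the interim at 49 and the futility bound recalculated (about 0.788 in place of 0.8443). The efficacy bound at half the information stays at 0.0031.
3. State that PFS is followed in every patient to a common cut-off, 5 years after the last randomization, so that the Study design section agrees with the sizing assumption.

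Neither option needs extra enrolment. The second moves the final analysis from about month 78 to about month 84 with 216 patients and no losses, which is the horizon the sizing already assumes. The common cut-off means collecting PFS beyond year 5 for patients who enter early.
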